##### IG counts

Whole blood cell counts will be performed on citrated whole blood using a Sysmex XN-1000 haematology analyser (Sysmex UK, Milton Keynes, UK), which defines IGs as promyelocytes, myelocytes and metamyelocytes within the white cell differential channel. Instrument performance will be ensured by daily measurement of quality control material (XN Check) and via participation in an external quality assurance scheme (UKNEQAS, Watford, UK).

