##### Neutrophil phagocytic activity

Neutrophil phagocytosis of fluorescently labelled opsonised *Escherichia coli* will be measured on heparinised whole blood using the commercially available PhagoTEST assay (BD Biosciences, Oxford, UK). To account for postburn leucocytosis, patient’s white cell counts will be normalised to those of HCs in order to ensure consistent leucocyte to bacteria ratios across all assays. By ‘quenching’ the fluorescent signal emitted from bacteria bound to the external plasma membrane of neutrophils, inclusion of a trypan blue staining step within this assay ensures that the fluorescent signal measured by flow cytometry is derived only from phagocytosed bacteria.

For the acquisition of raw data, a single flow cytometry template with specified gating plots and event limits will be used by all researchers analysing patient and HC blood samples. Gated based on their distinctive sideward scatter/forward scatter properties, a total of 10 000 neutrophils will be analysed and data relating to both the percentage of cells that have performed phagocytosis (% phagocytosis) and their mean fluorescence intensity (an indicator of the number of ingested bacteria per neutrophil) will be recorded. This information will then be used to calculate neutrophil phagocytic capacity using the following equation: (% phagocytosis/100) × mean fluorescence intensity.

Prior to flow cytometric analysis of all patient and HC blood samples, BD CS&T beads (BD Biosciences) will be run on the flow cytometer. These beads will ensure a standardised method of quality control will be performed on our instrument in respect to its optics, electronics and fluidics.

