##### CfDNA measurements

The concentration of total cfDNA), mitochondrial-derived DNA (mtDNA) and nuclear-derived DNA (nDNA) will be measured in platelet-free plasma (PFP) prepared from citrate anticoagulated blood samples. PFP will be stored at −80°C prior to analysis, which will be performed in two phases (phase 1: analysis of samples collected 1–28 days postburn; phase 2: analysis of samples collected at months 3–24 postburn).

Total cfDNA concentrations will be determined in duplicate PFP samples using an in-house SYTOX Green dye based fluorometric assay as described previously.^18^ Included within each assay will be: (1) a λ-DNA standard curve (0–1000 ng/mL) for calibration, (2) PFP samples from HCs, stored under the same conditions as our patient samples, to serve as reference values and (3) a ‘buffer only’ negative control. The mean fluorescence value derived from the negative control will be subtracted from all HC and patient data prior to the calculation of DNA concentration. A selection of patient and HC PFP samples will be analysed across assays to allow for the calculation of interassay and intra-assay coefficients of variation, which currently stand at 5.3% and 5.1%, respectively. Analysis of 32 PFP samples using our in-house assay quantified cfDNA to concentrations that were comparable to those measured using a CE-marked commercially available assay (Trillium Diagnostics; Spearman’s R=0.78, p<0.0001).

Using primer sets specific for the genes encoding cytochrome b and β-globin, real-time PCR will be performed to determine the concentration of mtDNA and nDNA, respectively.^18^ Included within each assay will be: (1) standard curves generated using DNA isolated from purified mitochondria and nuclei to enable quantification of mtDNA and nDNA concentrations, (2) DNA isolated from HC PFP samples, stored under the same conditions as our patient samples, to serve as reference values and (3) a ‘buffer only’ negative control. PFP samples from a selection of HCs and patients will be analysed across assays to allow for the calculation of interassay and intra-assay coefficients of variation. Our cytochrome b and β-globin primer sequences have no significant homology with DNA found in any bacterial species according to information provided by the Basic Local Alignment Search Tool.

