We will determine in how many participants the measurements of neutrophil phagocytic capacity, plasma cfDNA levels and IG count on day 1 of injury predicted a diagnosis of sepsis. This proportion will be reported along with 95% CIs calculated by binomial exact methods. The accuracy of this day 1 biomarker model will be determined through standard estimates of sensitivity, specificity, predictive values and likelihood ratios, with 95% CIs. We will investigate the value added by this day 1 biomarker test when compared with information obtained from other potentially informative sets of biomarkers (eg, revised Baux score). These combinations of tests will be assessed using logistic regression models. Using multivariable logistic regression analysis, we will also generate predictive probabilities for various combinations of these candidate biomarkers. This logistic modelling will aim to derive a prognostic regression function (ie, probability of sepsis) using the day 1 values of each candidate biomarker and other demographic or burn-related variables. Models of varying complexity may be compared through ROC analyses. Longitudinal data collection will enable us to examine how the performance of these models change over time. Limitations associated with the logistic regression approach lie mainly in its generalisability to other data sets. Thus, techniques such as bootstrapping to enhance generalisability will be applied for model validation. In sensitivity analyses, missing data will be estimated by multiple imputation and maximum-likelihood methods, as appropriate, in order to explore the potential bias and reduced statistical power associated with listwise deletion.

Serial sampling will allow for repeated measures analyses of our candidate biomarkers, enabling us to model their kinetics over time and examine how this differs between septic and non-septic patients. For the analysis of longitudinal data, continuous outcomes will be analysed using linear regression to compare the septic and non-septic groups, with mean differences and 95% CIs reported. For other outcomes, analysis of daily measurements will be performed using generalised linear mixed models to account for the hierarchical structure of the data. Summaries of model output will be provided with model effects presented both as estimates with associated 95% CIs and also, where appropriate, as plots to visualise the time course of fitted outcomes.

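### Repeated continuous biomarkers are assigned to plain linear regression while hierarchical models are kept for other outcomes, which conflicts with the repeated-measures aim

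*Protocol article*

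**What the plan says.** Three consecutive sentences in Data analysis matter. The first sets the aim: "Serial sampling will allow for repeated measures analyses of our candidate biomarkers, enabling us to model their kinetics over time", and goes on to how these kinetics differ between septic and non-septic patients. The second names the method for longitudinal data: "continuous outcomes will be analysed using linear regression to compare the septic and non-septic groups, with mean differences and 95% CIs reported". The third deals with the rest: "For other outcomes, analysis of daily measurements will be performed using generalised linear mixed models to account for the hierarchical structure of the data".

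Two of the three candidate biomarkers are clearly continuous. Phagocytic capacity is a proportion multiplied by a fluorescence intensity (Neutrophil phagocytic activity). cfDNA is a concentration: "Total cfDNA concentrations will be determined in duplicate PFP samples". IG count comes from an analyser ("Whole blood cell counts will be performed on citrated whole blood using a Sysmex XN-1000 haematology analyser"), and the article does not say whether it will be modelled as continuous or as a count.

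Data collection and patient outcomes lists 19 sampling times: 14 daily, day 28 and four late visits.

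**The concern.** The plan recognises that the data are hierarchical, yet attaches the models that handle this only to outcomes that are not continuous. Ordinary linear regression treats every row as independent. Sepsis group is a between-patient factor, so pooling a patient's repeated rows counts the same patient many times and understates the standard error of the group difference. That difference is the quantity the plan says it will report.

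The method is named rather than left open, so this is not detail that a protocol leaves to an analysis plan. The preceding paragraph of Data analysis does not repair it. For laboratory data across time points it names one-way ANOVA or Kruskal-Wallis with post hoc tests, and neither carries a patient effect.

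The comparison of immune kinetics between septic and non-septic patients is at stake. The article gives it as a reason for serial sampling and lists kinetic profiling among the study's strengths.

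**Working it through.** **Inputs from the protocol article.** 220 evaluable patients, sepsis prevalence 60%, 10% drop-out (Sample size); 14 daily samples, 19 in all (Data collection and patient outcomes); p<0.05 (Data analysis; two-sided assumed). No within-patient correlation ρ is given, so ρ is an assumption shown over a range.

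**Step 1: the plan's own figures.** 220 × 0.60 = 132 septic and 88 non-septic. The exact 95% CI is 0.836 to 0.945 for sensitivity 0.90 with n = 132, and 0.593 to 0.793 for specificity 0.70 with n = 88. The lower limits match the stated 84% and 59%. 220/0.90 = 244.4, rounded up to 245. The sample size reproduces. It rests on one set of day 1 values per patient, so the longitudinal model does not touch it.

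**Step 2: rows pooled, overall group difference, exchangeable correlation.** The design effect is DEFF = 1 + (m − 1)ρ, the standard error is too small by √DEFF, and the true type I error is 2(1 − Φ(1.96/√DEFF)). For m = 14 and ρ = 0.3, DEFF = 1 + 13 × 0.3 = 4.9 and √4.9 = 2.21.

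| m | ρ | DEFF | SE factor | Type I error | Coverage of a 95% CI |
|---|---|---|---|---|---|
| 14 | 0.1 | 2.3 | 1.52 | 20% | 80% |
| 14 | 0.3 | 4.9 | 2.21 | 38% | 62% |
| 14 | 0.5 | 7.5 | 2.74 | 47% | 53% |
| 14 | 0.7 | 10.1 | 3.18 | 54% | 46% |
| 19 | 0.3 | 6.4 | 2.53 | 44% | 56% |
| 19 | 0.5 | 10.0 | 3.16 | 54% | 47% |

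A simulation (2,000 runs, 132 and 88 patients, 14 days, no true difference) rejected in 37%, 49% and 53% of runs at ρ = 0.3, 0.5 and 0.7.

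**Step 3: same comparison, AR(1) correlation.** DEFF = 1 + 2 Σ(1 − k/m)ρ^k, summed over k = 1 to m − 1. With m = 14 this is 2.71 at ρ = 0.5 and 4.56 at ρ = 0.7, giving type I errors of 23% and 36%. The simulation gave 22% and 38%, and 14% at ρ = 0.3.

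**Step 4: the group-by-time slope, which is the kinetics term.** Under exchangeable correlation its true variance is (1 − ρ) times what pooled regression assumes, so the error is 2(1 − Φ(1.96/√(1 − ρ))): about 2% at ρ = 0.3 and 0.6% at ρ = 0.5 (simulated 3% and 0.7%). These intervals are too wide. Under AR(1) with ρ = 0.3, 0.5 and 0.7 the simulated error is 13%, 17% and 26%, so the intervals are too narrow. The term is miscalibrated either way, in opposite directions.

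**Step 5: alternatives.** A regression at a single time point rejected in 4% to 6% of runs, which is valid. Patient-clustered standard errors on the pooled rows brought the overall group test back to 5% to 6%.

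**The case against.** The strongest reply is that the article never says rows are pooled. It announces "Serial sampling will allow for repeated measures analyses of our candidate biomarkers" and speaks of daily measurements only in the mixed-model sentence. Linear regression could therefore mean one model per time point, or a summary per patient, and either gives valid intervals. This stands against any reading that the reported intervals are certain to be far too narrow; a reader might infer that, but the documents do not establish it. It does not rescue the wording. Per-day regression gives up to 19 separate comparisons and does not model kinetics, and neither a patient summary nor clustered standard errors is mentioned.

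A reader might also infer that chance differences in kinetics will generally be reported as significant. Step 4 shows that this holds under serial correlation but not under exchangeable correlation, where the kinetics term is conservative.

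The size is open to challenge too. The correlation is assumed, and 14 complete daily samples is a high case given deaths, discharge and drop-out. Table 2 allots children only 2 mL on seven of the first 14 days. If the full panel were run only on the eight larger-volume days up to day 28 (an assumption), DEFF would be 1 + 7 × 0.3 = 3.1 to 1 + 7 × 0.5 = 4.5, and the type I error 27% to 36%. That is smaller but still material.

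It is also tempting to say that all three biomarkers are affected. The article does not class IG count for modelling, so only phagocytic capacity and cfDNA can be claimed.

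Finally, the only stated objective is validation of early biomarkers, and it uses day 1 values. This stands in full and limits the weight of the point.

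**Conclusion.** The point holds as a conflict between a stated aim and a stated method, in a secondary analysis. As worded, the plan either miscalibrates inference on repeated continuous biomarkers (rows pooled) or does not model the kinetics it sets out to model (one regression per day), unless something unstated is added.

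In the pooled case, with 14 complete daily samples, the standard error of the overall group difference is too small by about 2.2 to 2.7 for exchangeable ρ of 0.3 to 0.5. The type I error is then about 37% to 47%, or about 22% to 38% under AR(1) with ρ of 0.5 to 0.7. These figures apply to unadjusted pooled regression and rest on assumed correlations.

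A reader might infer that the study's main conclusion is at risk. It is not: the day 1 sensitivity, specificity and logistic models use one set of values per patient, and the sample size reproduces. The change is worth making, but the primary analysis does not depend on it.

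**What to change.** Replace the linear regression sentence with a statement along these lines: repeated continuous outcomes, transformed where skewed, are analysed by a linear mixed model with a patient random effect or a structured residual covariance and fixed effects for sepsis group, time and group-by-time; model-based mean differences are reported with 95% CIs. Keep generalised linear mixed models for non-continuous outcomes, and say which class IG count falls in. Confine plain linear regression to analyses with one value per patient.

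The cost is a few lines of analysis text. No new data, visits or patients are needed. If pooling was intended, the intervals for the overall group difference will become wider. Those for the kinetics term may widen or narrow, depending on the correlation structure.

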### Data storage and retention

Following receipt of consent, patients will be assigned a sequential study number. This non-identifiable number will be used at all times to ensure patient confidentiality. A record of study numbers and patient details will be held at the Queen Elizabeth Hospital Research Office and will only be known to the chief and principal investigators and research personnel. The chief investigator of a particular research site will be responsible for the secure storage of all study related documents (eg, protocols, PIL, general practitioner (GP) letters, consent forms and CRF) in accordance with current International Council on Harmonisation Good Clinical Practice guidelines. All data and study related information will be stored for 15 years after completion of the study. All documents will be archived in accordance with the University Hospitals Birmingham Foundation Trust (UHBFT) archiving procedures.

### Patient and public involvement

Members of a patient and public involvement group were involved in discussions around the design of the study. The group were asked for their opinions on the frequency of patient blood sampling and provided input on the content of the PIL.

### Ethics and dissemination

The SIFTI-2 study received ethical approval from the West Midlands, Coventry and Warwickshire Research Ethics Committee on 7 June 2016 (REC reference: 16/WM/0217) and will be conducted according to the Declaration of Helsinki (2008). Findings from the study will be presented at national and international conferences, and submitted for publication in peer-reviewed clinical and academic journals.
